#### Patient profiling

To determine which patient characteristics may predict additional benefit of CBD augmentation, explorative multilevel analyses with treatment success as dependent variable will be performed, with the following independent variables (among others); medication (CBD or placebo), diagnosis (panic disorder with agoraphobia or social phobia), fear learning (response during extinction, and reduction of fear from acquisition to extinction), cannabinoid system genetics (using a candidate gene approach focused on CNR1 and FAAH), prior treatment history (failed CBT, SSRI, or both), clinical state at baseline and demographic variables (gender, age).

#### Fear learning

Acute effect of CBD on fear learning is analyzed with retention of conditioned fear, and rate of extinction in this re-extinction phase as outcome variables, and medication as independent variable. Impact of CBD-augmented exposure therapy on changes in rate of extinction from baseline between the CBD and placebo groups is examined by comparing extinction before and after treatment.

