### Randomization and blinding

The randomization (CBD or placebo) is conducted by an independent statistician using a computer algorithm, stratifying for study location and diagnosis (panic disorder with agoraphobia or social phobia). Patients are allocated to one of the medication groups after baseline measurements according to the order of patients in the stratum. Investigators, research assistants, therapists and participants will be blinded with respect to randomization. The capsules containing the different medications are identical in appearance except for filling which is either CBD or lactose (placebo). An independent data manager can break the randomization code in case of pregnancy, allergic reactions or any severe inexplicable symptoms. Apart from these circumstances, unblinding will not be done until after the last patient has completed the last follow up measurement.

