##### Experimental assessment of fear learning

To explore whether capacity for fear and extinction learning at baseline impacts the effect of CBD, and whether treatment with CBD has impact on improvements in extinction learning after treatment, an experimental fear conditioning and extinction task will be used to assess the capacity to acquire and extinguish conditioned fear [30]. At baseline, this task will investigate the acute effect of CBD on extinction learning, a second extinction phase with the same conditioned stimuli as at baseline is administered 2 h after the first ingestion of the medication. This additional fear extinction phase is administered 1 to 2 weeks after administration of the baseline fear conditioning task. Finally, post-treatment the same fear conditioning task will be administered, with minor adaptations to minimize previous learning effects (e.g. with different conditioned stimuli). With this post-treatment task, changes in rate of extinction due to treatment is compared between the CBD and placebo groups.

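### The exploratory acute-effect (re-extinction) analysis names medication as its only independent variable and leaves unused a pre-allocation measure on the same stimuli: valid, but less precise than it could be

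*Protocol article*

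**What the plan says.** Under Statistical analysis, Fear learning, the protocol article gives the acute-effect analysis one sentence. It begins "Acute effect of CBD on fear learning is analyzed with retention of conditioned fear" and goes on to "rate of extinction in this re-extinction phase as outcome variables, and medication as independent variable". No other term is named. The next sentence does use extinction before treatment, but for a different question: change in extinction rate from before to after therapy.

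The design supplies a baseline for the acute comparison. Under Experimental assessment of fear learning, "a second extinction phase with the same conditioned stimuli as at baseline is administered 2 h after the first ingestion of the medication". On timing, "This additional fear extinction phase is administered 1 to 2 weeks after administration of the baseline fear conditioning task". Table 1 places the task at T0, T1 and T3. Under Randomization and blinding, "Patients are allocated to one of the medication groups after baseline measurements according to the order of patients in the stratum", so the T0 record precedes assignment. That section also describes randomisation as "stratifying for study location and diagnosis (panic disorder with agoraphobia or social phobia"); fear learning is not a stratum.

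The Patient profiling analysis lists "fear learning (response during extinction, and reduction of fear from acquisition to extinction") among the predictors of treatment success, in a list expressly left open. The Fear learning sentence carries no such opening. The Background places the acute-effect question among the exploratory subsidiary aims.

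**The concern.** The T1 phase re-tests fear that each patient acquired and partly extinguished at T0. How much fear is present at T1, and how quickly it fades, plausibly depends on how that patient did at T0. The Background itself reports that extinction trajectories differ between patients and that patients are overrepresented in a poor-extinction profile.

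If T0 performance predicts T1 performance, a model with medication alone leaves that between-patient variation in the error term. The cost is a wider interval and lower power for one of the trial's mechanistic questions. If the arms happen to differ at T0, the unadjusted estimate also carries part of that difference and the plan names no step to remove it. Choosing covariates after unblinding would be a poor substitute, since it invites selective adjustment.

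**Working it through.** **Inputs from the protocol (Sample size).** 36 per arm; d = 0.6; error probability 0.05 (sidedness not stated, taken as two-sided); power 0.80; correlation 0.6 between repeated measurements, from clinical data and not from the conditioning task.

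**Assumed.** The T0-T1 correlation r of the task measures is not in the document; the range used is 0.2 to 0.6. The effect d = 0.6 is borrowed from the clinical outcome, since none is stated for this analysis.

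**1. The plan's own figure.** For a repeated-measures F test of the between-group factor, f = d/2 = 0.3, with m = 2 measurements:

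λ = N·m·f² / (1 + (m − 1)·0.6) = 72 × 2 × 0.09 / 1.6 = 8.1, df = (1, 70).

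Power is 0.801 at N = 72 and 0.790 at N = 70, so the stated 72 reproduces. That calculation concerns the clinical outcome; no sample size or power is stated for the acute-effect analysis.

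**2. Power of the acute comparison.** Two-sample t test: noncentrality = d·√(n/2) = 0.6 × √18 = 2.55, df = 70, power 0.71. With one T0 covariate the residual SD is multiplied by √(1 − r²), so noncentrality = 0.6·√18 / √(1 − r²), df = 69:

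| r (assumed) | Residual variance, 1 − r² | Reduction | Power |
|---|---|---|---|
| medication only | 1.00 | – | 0.71 |
| 0.2 | 0.96 | 4% | 0.73 |
| 0.3 | 0.91 | 9% | 0.75 |
| 0.4 | 0.84 | 16% | 0.78 |
| 0.5 | 0.75 | 25% | 0.83 |
| 0.6 | 0.64 | 36% | 0.88 |

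A simulation of 40,000 trials agrees. Medication-only power was 0.71 at both r = 0.3 and r = 0.6; adjusted power was 0.74 and 0.88.

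**3. Validity of the unadjusted test.** With no treatment effect, the same simulation gave type I error of 0.049 (r = 0.3) and 0.050 (r = 0.6) for medication only, and 0.050 in both cases with adjustment. Averaged over randomisation, nothing is wrong with the unadjusted test.

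**4. Given a realised imbalance.** The standard error of the T0 difference between arms is √(2/36) = 0.24 SD. The unadjusted estimate shifts by r × imbalance. Conditional type I error (normal approximation) is:

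- r = 0.6, imbalance of 1 SE (0.24 SD): shift 0.14 SD, type I error 0.045.
- r = 0.6, imbalance of 1.96 SE (0.46 SD): shift 0.28 SD, type I error 0.16.
- r = 0.3, imbalance of 1.96 SE: shift 0.14 SD, type I error 0.08.

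**5. Change score as an alternative.** With equal variances at T0 and T1, a plain change score has variance factor 2(1 − r): 1.4 at r = 0.3 and 0.8 at r = 0.6, against 0.91 and 0.64 with covariate adjustment. Simulated power was 0.57 and 0.81. At r = 0.3 the change score is therefore worse than no adjustment (0.71), and at r = 0.6 it still falls short of adjustment (0.88).

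**The case against.** The strongest reply is that one sentence in a condensed article names the outcomes and the treatment factor, and does not say that the model is unadjusted; covariates may stand in a full protocol or analysis plan that is not shown. That possibility remains. But the sentence names one independent variable, while the Patient profiling list just before it is left open. As written it describes a medication-only model, and it does not defer the choice to another document.

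Four further replies limit the point, and all stand.

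- A reader might infer that the analysis will mistake chance differences in baseline fear learning for a CBD effect. The documents do not support that. T0 precedes allocation, and the standard error of the unadjusted comparison already allows for chance imbalance. The shift exists only conditional on an imbalance that has occurred.
- Retention of conditioned fear is not defined and may already be scored against T0. It cannot be said that baseline is ignored for that outcome. The point is firmest for the rate of re-extinction.
- A reader might take this as the trial's only test of an acute mechanism. The protocol also uses distress ratings within sessions to measure extinction, and secondary measures at T1 and T3 to study acute effects.
- Both numbers behind the size are borrowed or assumed. At r = 0.2 the gain in power is about 2 points, and nothing in the document shows that r is higher for this task.

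**Conclusion.** The point holds as one of precision, not validity. The stated model leaves unused a relevant measure taken before allocation on the same stimuli. At d = 0.6 and 36 per arm, adjusting for it would raise power from 0.71 to 0.73 at r = 0.2 and to 0.88 at r = 0.6. It would also remove the r × imbalance shift if the arms differ at T0. These sizes rest on an assumed r, a borrowed effect size, a two-sided 5% test and complete data on 36 patients per arm. Severity is minor, because the aim is exploratory and the trial was not sized for it.

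**What to change.** Amend the acute-effect sentence under Fear learning so that each T1 outcome is analysed by a linear model with medication, adjusted for the corresponding measure from the T0 task:

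- **Rate of re-extinction:** adjust for the T0 rate of extinction.
- **Retention:** use the T1 level of conditioned response as the outcome, adjust for the conditioned response at the end of T0 extinction, and do not rely on a plain change score. State this as the definition of the retention index.

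The cost is one degree of freedom per model. The two T0 indices must be derived from data already recorded; they are not exactly the fear-learning variables named under Patient profiling, so this is a small extra step. Patients with an unusable T0 record need simple imputation of the covariate to stay in the analysis. The change should be fixed before unblinding.

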#### Cost effectiveness

Costs of illness and intervention is measured using resource utilization which will be valued with unit costs based on standardized real cost price calculations. The economic evaluation is primarily designed as exploratory cost-effectiveness analyses.

### Data management and dissemination

To improve data completeness we have developed a study specific digital file to store personal information and to get reminders for upcoming assessments and missing data, which can be accessed by the researchers per participating center. Actual data are not collected in this file, but stored digitally in a database on the servers of GGZinGeest, separately from personal information of the participants. To ensure data quality and reliability, questionnaires are administered online and saved digitally, together with and data from interviews. Data from treatment sessions is collected and entered into the study data base and subsequently checked by research assistants. Data management and monitoring is conducted by data managers from GGZinGeest. Study conduct is reported and audited in interim, with final reports to the funding agency. The procedures comply with Dutch data privacy laws.

If participants wish to withdraw from the intervention, their participation in the post-treatment and follow up assessments are encouraged. Unless participants have withdrawn consent for follow-up, repeated attempts are made to contact participants. In a step-wise manner, this will involve sending emails and calling the individual on contact numbers provided on various days of the week and at different times. As much information as possible will be collected from protocol non-adherers.

Adverse events occurring after entry into the study are recorded. Investigators will determine relatedness of an event to the study drug based among others on temporal relationship and the subject’s clinical course.

Any modifications to the protocol which may impact the conduct of the study, potential benefit of the patient or may affect patient safety, including changes of study objectives, study design, patient population, sample sizes, study procedures, or significant administrative aspects will require a formal amendment to the protocol. Such amendment will be approved by the Ethics committee prior to implementation and information on the Trial register website will be updated to ensure transparency.

There are no interim analyses planned. The final trial dataset will be accessible to the researchers and data managers. Results of the analyses will be published in scientific journals and presented on scientific conferences by the researchers, regardless of the outcome. A summary report of trial results written in lay language will be sent to study participants and other people who have expressed interest.

## Discussion

Phobic disorders are among the most prevalent disorders and have a major impact on the life of patients and society as a whole resulting in suffering and associated costs. Evidence-based treatments of these disorders, while effective for a large number of patients, are not adequate for a substantial group who are not sufficiently relieved from their anxiety symptoms. One strategy may be to boost the effectiveness of current treatments. Enhancing exposure therapy with pharmacological agents that affect the neurological processes involved in the extinction of fear is an avenue that has been explored with augmentation using d-cycloserine, with mixed success [68]. Since an enhancer of exposure therapy is needed but the compounds so far have not proven to be sufficiently effective, we have opted to use a new strategy using the modulation of the endocannabinoid system. This study will be the first clinical trial in which cannabidiol is used to augment exposure therapy for phobic patients.

It is important to note that this study is investigator initiated, and independent from pharmaceutical or other industry interests. Findings will be submitted to a peer reviewed scientific journal for publication.

This study is based on the preclinical evidence that ECS manipulations can be used to enhance (the retention of) fear extinction. However, acute anxiolytic effects of cannabidiol have also been reported. One study reported anxiolysis during a public speaking challenge, which resembles the type of challenges that patients with phobia are faced with during exposure therapy [69]. Hence, an additional possible outcome of the study is that cannabidiol reduces fear and anxiety acutely during the treatment sessions, making the treatments easier to tolerate. Despite the conviction based on other anxiolytic treatments that anxiolysis during exposure reduces effectiveness [70], the expectation is that cannabidiol may combine acute anxiolysis with enhanced retention of treatment effects.

A strong feature of this study is the exploratory assessment of genetic, experimental and clinical differences between patients related to extinction and subsequent treatment response. The results of this study might give rise to new insights into the possibility of personalized treatment, by exploring whether this strategy is best, specifically for patients with certain characteristics.

## Abbreviations

5-HT1A: Serotonin 1A
ACQ: Agoraphobic cognitions questionnaire
AQ: Autism spectrum quotient
BAI: Beck anxiety inventory
BDI: Beck depression inventory
BSQ: Bodily sensations questionnaire
CB1: Cannabinoid 1
CBD: Cannabidiol
CBT: Cognitive behavioral therapy
CGI: Clinical global impression
CTQ: Childhood trauma questionnaire
ECS: Endocannabinoid system
EQ5D: EuroQol 5D
FAAH: Fatty acid amide hydrolase
FQ: Fear questionnaire
LSAS: Liebowitz social anxiety scale
MI: Mobility inventory
NLV: Nederlandse leestest voor volwassenen
PDSS: Panic disorder severity scale
SCID: Structured clinical interview on DSM-IV disorders
SPAI: Social phobia and anxiety inventory
SSRI: Selective serotonin re-uptake inhibitor
SUDS: Subjective units of distress scale
THC: Delta-9-tetrahydrocannabinol
Tic-P: Trimbos and iMTA questionnaire on Costs associated with Psychiatric illness
TRPV1: Transient receptor potential vanilloid type 1
VAS: Visual analogue scale
